#### Participants assigned to intervention group

Participants allocated to the intervention group also receive the usual health service-provided smoking cessation support, as above. In addition to this they are provided with smoking cessation counselling at face-to-face visits, which will be scheduled weekly for the first four weeks, monthly to 6 months and two monthly to 12 months. During the intervention the Aboriginal researchers are to concentrate on smoking cessation. Face-to-face follows up can take place at the clinic or other location suitable to the participant (e.g. home, work). While face-to-face contact is the default option, this may have to be adjusted if a participant's circumstances makes this difficult (e.g. a full-time worker may be offered phone contact for some of the follow up visits). If a participant does not attend for a follow up visit, the Aboriginal researcher is to initiate active follow up within 48 hours through phone or home visit to determine the reason for non-attendance and where possible determine solutions to encourage ongoing participation.

Participants in the intervention group are also encouraged to participate in a monthly smoking cessation support group, which include: 1) additional smoking cessation support and advice including cognitive and behavioural approaches to 'quitting'; 2) opportunities for information sharing/sharing of barriers and solutions; 3) a light healthy meal and 4) information sharing and advice on other aspects of health and well-being including management and prevention of common chronic diseases, which will be delivered by appropriately trained people. The group therapy occurs at both sites. This is a rolling group, with participants continually entering and leaving the group.

Content to be delivered by Aboriginal researchers:

• Individual

○ Motivational interviewing (e.g. what do you like/do not like about smoking)

○ Triggers for smoking/diversions & strategies to deal with them

○ Action plans - preventing and dealing with short term relapses (termed 'slipups')

○ Discussion regarding the positives of smoking cessation (e.g. saving money)

○ Pharmacotherapy (e.g. NRT)

○ Identification of factors driving smoking and case management to link participants to additional non-health service, community-based support agencies (e.g. alcohol counselling)

○ Smoking cessation-associated weight gain - generic discussions regarding potential weight gain and providing education and advice (e.g. 'healthy' eating, exercise)

• With the health care clinic medical officer/general practitioner

○ Organise weekly case conference to review all active participants in the intervention group

• Monthly group meeting

○ Researcher conducted

○ Including dietician input for associated weight control advice

• Service mapping and linkages

○ Identify and develop referral networks to help address consequences of tobacco cessation and drivers of tobacco consumption (e.g. alcohol, domestic violence, stress, mental illness, weight changes, etc.)

### Outcome measures

Primary endpoint:

• The proportion of participants who were not smoking tobacco at 12 months as determined by self-report and urinary cotinine level consistent with no recent tobacco consumption [26].

Secondary endpoints:

• The proportion of participants who were not smoking at 6 months as determined by self-report.

• The proportion of participants reporting excellent or very good health using a self-reported health questionnaire [27].

• The proportion of participants who reported 20% or greater reduction in the number of cigarettes smoked each week.

• Process evaluation indicators: a mix of quantitative and qualitative measures to assess how well the intervention program was implemented according to the protocol e.g. number of 'face-to-face' meetings completed, challenges and solutions in delivering the program.

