#### Participants assigned to the control group

Participants allocated to the control group receive the usual practice of the service, including but not limited to advice from clinical staff regarding the harmful effects of smoking, advice regarding quitting, pharmacotherpay, self-initiated follow up, and access to usual services offered by the service (e.g. at DAHS clients are offered participation in lifestyle and primary prevention education classes).

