### Sample size

The sample size estimation is based on a two-sided alpha of 0.05, beta of 0.2 (power 0.8), ratio of intervention to control participants of 1:2, and efficacy of maintaining smoking cessation at 12 months of 3% in the control group and 13% in the intervention group. Based on these assumptions the sample size required will be 106 in the intervention group and 212 in the control group across both sites. Using a conservative estimate of 50% of the clients being smokers, we will be recruiting less than 20% of regular DAHS and OVAHS clients for the trial. To take into account those lost to follow up (e.g. deaths), the aimed sample size is 120 in the intervention group and 240 in the control group across both sites.

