## Abbreviations

ACCHS: Aboriginal community controlled health service; BOABS: Be our ally, beat smoking; DAHS: Derby aboriginal health service; DSMC: Data safety and monitoring committee; HREC: Human research ethics committee; NRT: Nicotine replacement therapy, available in a range of forms such as patch, gum lozenges, tablets and nasal spray; NHMRC: National health and medical research council; OVAHS: Ord valley aboriginal health service; RCT: Randomised controlled trials.

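### Urinary cotinine also rises with nicotine replacement, so 12-month quitters still using it can be scored as smokers in the primary endpoint

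*Protocol article*

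**What the plan says.** Under Outcome measures, the primary endpoint is the proportion not smoking at 12 months "as determined by self-report and urinary cotinine level consistent with no recent tobacco consumption". Both conditions must hold. The Abstract and Study design sections give the same two-part definition, and none of the three mentions participants who use a nicotine product. The cotinine criterion cites a reference that is not shown, and the article prints no cut-off.

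The content the researchers deliver individually to the intervention group includes "Pharmacotherapy (e.g. NRT" as the example given. The Abbreviations section describes it as "NRT: Nicotine replacement therapy, available in a range of forms such as patch, gum lozenges, tablets and nasal spray". Visits are scheduled "weekly for the first four weeks, monthly to 6 months and two monthly to 12 months", so contact lasts until the primary endpoint is measured.

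Controls are not cut off from pharmacotherapy. Usual care includes "advice regarding quitting, pharmacotherpay, self-initiated follow up", and intervention participants "also receive the usual health service-provided smoking cessation support, as above".

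The section on planned recruitment and loss to follow-up says that a reduced form was created because participants found the 6- and 12-month questionnaires hard to complete. Neither form is shown.

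**The concern.** The biochemical test is meant to detect tobacco, but what it measures comes from nicotine of any source. That is a general property of the marker; the article does not state it. The intervention itself covers a nicotine product, so part of the treatment can make its own success look like failure.

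Each such misclassification removes a true quitter. More quitters are expected in the intervention arm, so even an equal share lost in both arms narrows the risk difference. If use at month 12 is higher in the intervention arm, the ratio of quit rates is biased towards no effect as well. Events are few: 13% of 106 is 13.8 quitters and 13% of 120 is 15.6. Losing two or three of them matters.

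There is also a timing problem. A classification rule can be written later, but NRT use that nobody recorded when the urine was taken cannot be recovered.

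**Working it through.** **Inputs from the Sample size section.** "two-sided alpha of 0.05, beta of 0.2 (power 0.8), ratio of intervention to control participants of 1:2"; 12-month cessation of "3% in the control group and 13% in the intervention group"; 106 intervention and 212 control participants required, 120 and 240 to be recruited.

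**The plan's own figure.** The pooled-variance two-proportion formula with these inputs gives 79/158 without and 93/186 with continuity correction, not 106/212. The corrected formula gives 212/106 if the ratio is reversed, with the larger arm at 13%. That discrepancy is a separate matter. Here it means only that 106/212 starts with more than 80% power.

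**Assumption.** The documents give no rate of NRT use at 12 months. Let f_I and f_C be the shares of true quitters who are cotinine-positive from NRT alone. Observed rates are then 0.13(1 − f_I) and 0.03(1 − f_C).

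**Test and power.** With x quitters of n1 = 106 and y of n2 = 212, and p̄ = (x + y)/(n1 + n2), reject when

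(|x/n1 − y/n2| − ½(1/n1 + 1/n2)) / √[p̄(1 − p̄)(1/n1 + 1/n2)] > 1.96.

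Power is the sum of Bin(x; n1, p1) × Bin(y; n2, p2) over all rejecting pairs (x, y), so it is exact for this test.

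| f_I | f_C | Intervention | Control | Difference | Ratio | Power, corrected | Power, uncorrected |
|---|---|---|---|---|---|---|---|
| 0 | 0 | 13.0% | 3.00% | 10.00 points | 4.33 | 0.877 | 0.917 |
| 10% | 5% | 11.7% | 2.85% | 8.85 points | 4.11 | 0.818 | 0.871 |
| 20% | 5% | 10.4% | 2.85% | 7.55 points | 3.65 | 0.712 | 0.784 |
| 30% | 5% | 9.1% | 2.85% | 6.25 points | 3.19 | 0.574 | 0.662 |
| 10% | 10% | 11.7% | 2.70% | 9.00 points | 4.33 | 0.837 | 0.886 |
| 20% | 20% | 10.4% | 2.40% | 8.00 points | 4.33 | 0.783 | 0.845 |
| 30% | 30% | 9.1% | 2.10% | 7.00 points | 4.33 | 0.714 | 0.792 |

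With f_I = f_C = f, the difference becomes (0.13 − 0.03)(1 − f): it shrinks by the factor (1 − f) while the ratio stays at 4.33. With f_I > f_C, both shrink.

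At the recruitment target of 120/240 with no loss, corrected power is 0.86 for 10% against 5% and 0.76 for 20% against 5%.

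**The case against.** **The article may not fix a wrong rule.** The criterion speaks of tobacco rather than nicotine and rests on an unseen reference, which, like the full protocol, may say how NRT users are handled. The 12-month forms may already ask about NRT. This stands as a limit on certainty, and a reader should not infer that no NRT rule exists anywhere. It does not remove the point: the definition appears three times without an exception, the intervention covers NRT, and a gap in data capture cannot be repaired at analysis.

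**A difference between arms is not documented.** It is tempting to say that genuine quitters on NRT will fail more often in the intervention arm. The documents do not support that as a fact. Controls may receive pharmacotherapy too, no extra provision to the intervention arm is stated, and a visit schedule running to month 12 is not evidence of NRT use at month 12. Greater use there is plausible, given repeated counselling on it, and no more than that.

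**The size depends on chosen shares.** This is correct. With 10% against 5%, power is still 0.82, above the planned 0.80. Only the larger shares do serious harm. The Sample size section also does not say whether 13% and 3% are true or cotinine-validated rates; if validated, the deflation above counts some of the loss twice.

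**Accepting self-report from NRT users has its own bias.** The trial is open, and the researchers who deliver the intervention also administer the questionnaires. Waiving validation could add unverified successes, possibly more of them in the intervention arm. This stands, and the fix allows for it.

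**Conclusion.** The point holds in a limited form. Followed as written, the primary endpoint can score abstinent NRT users as smokers. The resulting bias in the risk difference is towards no effect, whether or not the arms differ in NRT use; the ratio of quit rates is biased only if they do differ.

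The size cannot be known from the documents. It depends on NRT use among true quitters at the 12-month urine sample, not during the programme. Under the assumed 10% to 30% of intervention and 5% of control quitters, corrected power at 106/212 falls from 0.88 to between 0.82 and 0.57; with 10% in both arms it is 0.84. If use at month 12 is rare, the effect is small. These figures treat 13% and 3% as true quit rates.

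This should be settled before the 12-month data are analysed, and the recording part before the remaining 12-month samples are taken.

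**What to change.** 1. Add one question on use of any nicotine product in the previous 7 days to both the full and the reduced 12-month forms, in both arms, answered when the urine sample is arranged. If the forms already ask this, say so.
2. Before analysis, prespecify how self-reported abstainers who report NRT and have raised cotinine are classified.
3. Report the primary result both ways: with raised cotinine always counted as smoking, and with NRT users classified by self-report. Give the number of participants affected in each arm.

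The cost is one question and one extra analysis. The self-report version is unverified in an open trial, so it belongs beside the strict version and should not replace it. Together the two show how far the result depends on these participants. No treatment changes.

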### Randomisation: allocation, concealment and sequence generation

Block randomisation (36 participants per block × 6 blocks) is used to randomly assign participants to Group 1 (control group) or Group 2 (intervention group). Each site has 216 envelopes allocated. Each block has 24 participants randomly assigned to Group 1 and 12 to Group 2 using a computer generated random list of dichotomous outcomes (control or intervention) generated for each site using Excel 2007 software (Microsoft, Redmond, WA, USA). While only 5 blocks are required an extra block is generated to allow for contingencies that might require extra participants to be recruited. Envelopes are filled and sealed by an individual who is not involved with the study or its analysis. Envelopes are kept off-site and under the supervision of administrative staff based at a centralised coordinating site (the Kimberley Aboriginal Medical Services Council in Broome). Allocation occurs via telephone with envelopes being opened in sequential order for each site only once a participant is consented and enrolled in the study, eligibility is confirmed, an identification number is, assigned and the first questionnaire completed.

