### Proposed intervention

Participants are told that they will be randomly assigned to a group that receives 'usual care', or a group that receives extra support visits by an Aboriginal smoking cessation officer, and that a questionnaire will be administered when they enrol, and at six and 12 months following enrolment.

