### Planned recruitment rate and risk of loss to follow up

We aim to recruit 12 people (approximately 8 control, 4 intervention) monthly for 15 months. This regular staggered recruitment is to ensure that a maximum of 38 participants will be followed up by the four half-time Aboriginal researchers in any one week period. This will allow for variations to the scheduled recruitment without placing too much pressure on resources. The trial should be completed in 26 months.

As it proved difficult for participants to complete the original six and 12 month questionnaires, an alternative, minimal data collection tool was created. If participants leave Derby or Kununurra the Aboriginal researchers attempt to administer the final questionnaire by alternate means (e.g. phone, Facebook) and arrange for a local health care clinic to collect urine samples.

If recruitment of 360 participants (120 intervention and 240 control) is proving difficult within the time frame of the trial, an interim analysis of primary endpoints will be performed. It should be noted that the requirement for an interim analysis will be at the discretion of the investigators and anticipated speed of recruitment. If required, an interim analysis is to be undertaken by the Data Safety and Monitoring Committee (DSMC) once 50% of the participants (60 in the intervention and 120 in the control group) have completed the study. If this demonstrates a difference that is deemed by the DSMC to be statistically and clinically significant then the DSMC will provide advice to the supervising Human Research Ethics Committees (HREC) regarding whether the trial should be terminated.

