### Data analyses

Data from the trial will be entered into the database described above and then extracted into Stata, version 12 (StataCorp, College Station, Tex, USA). Analysis of questionnaire data will be descriptive and utilise univariate parametric and non-parametric analysis to identify differences between the control and intervention group and the intervention group prior to and following the intervention.

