### Baseline characteristics

All known potential confounders will be measured at baseline, including sex, age, education level, marital status, and smoking status of partner and other household members. Thus, comparisons of the intervention and control groups will be performed both unadjusted and adjusted for these known confounders. This second adjusted analysis will control for any maldistribution after randomisation of the confounders between the two groups.

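### Baseline self-rated health is not named as a covariate for the self-rated health endpoint; adjusting for it would be a free, minor gain in precision

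*Protocol article*

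**What the plan says.** Under Outcome measures, the protocol article gives as a secondary endpoint "The proportion of participants reporting excellent or very good health using a self-reported health questionnaire". This is a level, with no reference to the answer at enrolment.

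Three places bear on how it is analysed:

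- **Data analyses** sets the method for questionnaire data: "univariate parametric and non-parametric analysis to identify differences between the control and intervention group and the intervention group prior to and following the intervention". The between-arm part is univariate. The only comparison that uses pre-intervention answers is a before/after contrast within the intervention arm.
- **Baseline characteristics** says that comparisons of the groups will be "performed both unadjusted and adjusted for these known confounders", the confounders being introduced as "including sex, age, education level, marital status, and smoking status of partner and other household members". Baseline health is not named.
- **Treatment effects** says only that secondary outcomes will be analysed by standard procedures for categorical or continuous data.

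On timing, Proposed intervention says that "a questionnaire will be administered when they enrol, and at six and 12 months following enrolment", and the Randomisation section opens the envelope only after consent, confirmation of eligibility and having "the first questionnaire completed".

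**The concern.** A participant who already rates their health as excellent or very good at enrolment is more likely to do so again at follow-up, in either arm. Part of the spread in the follow-up answer can therefore be predicted before allocation, and is probably predicted better by the same question asked at enrolment than by any named covariate. Block randomisation is generated for each site, so nothing in the design balances baseline health between the arms.

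If the baseline answer stays out of the randomised comparison, the confidence interval is wider than the collected data require. In a trial where the arms happen to differ noticeably at baseline, part of that gap also carries into the follow-up difference, and the named covariates may not remove it. The stake is precision on one secondary endpoint.

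**Working it through.** **What the article supplies.** The Sample size section gives 106 intervention and 212 control participants as the number required, and 120 and 240 as the recruitment target, with two-sided alpha 0.05. These figures were set for the quit rate. No prevalence, effect size or correlation is given for self-rated health, so there is no stated figure to reproduce and the values below are assumptions: prevalence p = 30% or 35%, and baseline-to-follow-up correlation r = 0.3 to 0.5.

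**Step 1: precision without adjustment** (106 v 212, p = 0.30).
SE = √[0.30 × 0.70 × (1/106 + 1/212)] = 0.0545, so the 95% half-width is 1.96 × 0.0545 = 10.7 percentage points.

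**Step 2: precision with adjustment.** Adjusting for a baseline value with correlation r multiplies the variance by about 1 − r². The equivalent unadjusted total is 318/(1 − r²).

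| r | Variance reduction | 95% half-width | Equivalent unadjusted total |
|---|---|---|---|
| 0 | 0% | 10.7 points | 318 |
| 0.3 | 9% | 10.2 points | 349 |
| 0.5 | 25% | 9.3 points | 424 |

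The proportionate reduction does not depend on the size of the effect. If r were 0.7, it would be 49%.

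**Step 3: power.** The gain in power does depend on the effect. A simulation with 6,000 replicates per scenario (120 v 240, p = 0.35, r = 0.5) compared the unadjusted test with a baseline-adjusted regression. The SD of the estimate was 0.0549 unadjusted and 0.0483 adjusted.

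- True difference of 15 points: simulated power 0.781 v 0.873, a gain of about 9 points.
- True difference of 5 points, from the same SDs: Φ(0.05/0.0549 − 1.96) = Φ(−1.05) ≈ 0.15, against Φ(0.05/0.0483 − 1.96) = Φ(−0.92) ≈ 0.18, a gain of about 3 points.
- True difference of 15 points with r = 0.3: 0.781 v 0.819, a gain of about 4 points.

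**Step 4: validity.** With no true effect, p = 0.30, 106 v 212 and 100,000 simulated trials, the unadjusted test rejects in 5.0% of trials at r = 0.3 and 5.1% at r = 0.5. Overall type I error is not inflated.

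**Step 5: trials with a chance imbalance.** A baseline gap of 10 points or more, in either direction, arose in about 6% of those trials. About r times the gap carries over, so 10 points at baseline becomes 3 points (r = 0.3) to 5 points (r = 0.5) at follow-up. Within those trials the unadjusted test rejects 9% of the time at r = 0.3 and 18% at r = 0.5. When the gap is below 3 points it rejects less than nominally (4.2% and 2.6%), which is how the overall rate stays at 5%.

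**The case against.** The case for leaving the text alone has four parts.

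- **The method is still open.** Treatment effects leaves secondary outcomes to standard procedures, the confounder list is introduced as open-ended, and covariates for a secondary outcome are often fixed in an analysis plan that is not shown here. A reader might infer that the plan adjusts for social factors alone and shuts baseline health out. The text does not support that: age and sex are listed, and baseline health is unnamed, not excluded. The point survives in narrower form, because the article does commit questionnaire data to univariate comparison and does name covariates, and the obvious one for this endpoint is not among them.
- **Collection at enrolment is inferred.** No sentence says that the health item is in the enrolment questionnaire. The before/after analysis implies that pre-intervention questionnaire data exist, which makes it a reasonable inference but not a certainty. In addition, for follow-up "an alternative, minimal data collection tool was created", and the article does not say whether it keeps the item. This stands, and the fix has to be conditional.
- **Randomisation already protects the comparison.** A reader might infer that chance baseline differences will be mistaken for program effects as a general matter. They will not: the unadjusted estimate is unbiased, its interval allows for chance imbalance, and type I error is about 5%. This stands; only the conditional problem in Step 5 and the loss of precision remain.
- **Large power gains rest on large assumed effects.** The Sample size section assumes only a 10-point difference in quitting (3% v 13%), so a 15-point shift in self-rated health is optimistic, although the program has other health content. For a 5-point difference the gain is about 3 points. This stands for power, but not for the variance reduction.

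**Conclusion.** The point holds as one of efficiency, with minor weight. As written, the between-arm analysis of self-rated health is univariate or adjusted for a named set that does not mention the participant's own baseline answer, although that answer would be a legitimate pre-randomisation covariate if it was collected.

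Under an assumed correlation of 0.3 to 0.5, the variance given up is about 9% to 25%. The matching gain in power runs from slight to about 9 points, according to an effect size that the article does not state. The unadjusted comparison remains a valid test, so this is not an error of validity, and it concerns one secondary endpoint only.

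**What to change.** Add one statement across Data analyses, Baseline characteristics and Treatment effects:

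- The between-arm analysis of self-rated health will be a logistic regression of the follow-up answer (excellent or very good, yes or no) on arm and the participant's baseline self-rated health, where the item was collected at enrolment.
- The result will be reported as a standardised risk difference with a 95% confidence interval.
- A missing baseline answer will be handled with a missing-category indicator, so that no participant is dropped for lacking it.
- The unadjusted proportions will be kept as description.

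Before adding it, confirm that the enrolment questionnaire contains the item. Fix the statement before outcome data are seen, so that the adjustment cannot look chosen after the fact. If the item was collected, the cost is one sentence and one extra covariate in one model, with no new data, visits or participants.
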